### Assignment of interventions and collection

Written information with a consent form is given to all nulliparous women during pregnancy. When they have signed consent, these women may be included in the study at birth if they fulfil inclusion criteria.

Randomization is open, (not blinded). Randomization is computer-based, supported from the Unit for Applied Clinical Research at the Norwegian University of Science and Technology (NTNU). At randomization, the women are stratified according to body mass index (BMI), because obesity influences almost all aspects of pregnancy and labour. The groups are stratified according to first trimester BMI: BMI < 25, BMI 25–30 or BMI > 30.

### Collection of data

A flow chart (Figs. 1 and 2) guides the midwives through different procedures, before and during delivery and follow-up. Blood samples are collected for later analyses of hormones and cytokines to explore them as risk markers/indicators for prolonged labour. They will be centrifuged and stored in a freezer at −80 degrees.

**Fig. 1 Fig1:**
[figure not shown]
Flow chart for midwives in the delivery department. *g.w*. gestational week

**Fig. 2 Fig2:**
[figure not shown]
Flow chart for midwives in the delivery department, in details edition

According to the flow chart, after 12 hours, the midwife will, together with the gynaecologist on call, evaluate instrumental delivery if there is insufficient progress. According to Reuwer et al., if the flow chart is followed, this will rarely be necessary [7].

The midwife who is responsible for the woman in labour collects written consent upon arrival. In Norway, all pregnant women have a health card for follow-up throughout their pregnancy. The health card is collected upon arrival at the hospital. The documentation during labour and postpartum is performed by an electronic medical file system (Doculive: Cerner Sverige AS company EPJ© and Natus: Natus Medical Incorporated ©). For the participants in the present study, the midwife will additionally report study-specific data in a structured form.

The project coordinator midwife will collect the data from the study form, the health card and from the participants’ medical files. A case report form (CRF) has been prepared in cooperation with the Unit for Applied Clinical Research at the NTNU. All data relevant for the study will be registered in the CRF. The CRF is electronic and web-based.

Maternal satisfaction with the birth experience will be assessed by the validated CEQ questionnaire. This questionnaire will be mailed to the mothers 6–8 weeks after birth. The mothers will be asked to return the form in a post-paid envelope.

### Statistical analyses

#### Power calculation

There are around 4000 deliveries per year at St Olav’s University Hospital of Trondheim. Approximately 1500 are nulliparous women. Among these, 10% are estimated to have protracted delivery. About 150–200 nulliparous women per year are expected to meet the inclusion criteria. We assume that the proportion of pathological births in this group is about 30%. To detect a 50% reduction in pathological births in the proactive group with 80% power, we will need 120 women in each group (http://clincalc.com/stats/samplesize.aspx).

##### Study variables

Baseline variables are: (1) age, (2) civil status, (3) education and (4) former gynecological history (miscarriage, extra uterine pregnancy).

Variables reported during labour are: (1) number of vaginal examinations, (2) use and dosage of oxytocin before the baby is born, (3) use of spinal/epidural analgesics, (4) episiotomy, (5) mode of delivery, (6) haemorrhage, (7) perineal lacerations and (8) duration of labour.

New-born variables are: (1) weight, length and head circumference, (2) Apgar score at 5 and 10 minutes and (3) number of transmissions to neonatal intensive care unit.

The CEQ includes 22 items formulated as positive and negative statements. Each item will provide one variable in the data collection. The response format has a 4-point Likert scale, ranging from 1– totally agrees, 2 – mostly agree, 3 – mostly disagree, 4 – totally disagree. Memory of labour pain, sense of security and control are assessed with visual analogue scale (VAS). The VAS scores will be transformed to categorical values. Each item will provide one variable in the data collection [15].

No interim analyses are planned. Both types of management of labour are practiced in Norway.

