**Methods/Design:**

A prospective, non-blinded, randomized, single-centre, clinical trial where we compare proactive support to standard support of labour in a university hospital setting.

Inclusion criteria: latent phase of labour, non-pathologic pregnancy. Robson group 1, with painful contractions, and fully effaced cervix, with 1–3 cm dilatation. Exclusion criteria: induction of labour, breech presentation, twin pregnancy, multi-parity, conditions that require extended surveillance before and/or during labour.

Primary outcome: spontaneous, uncomplicated vaginal delivery. After inclusion, women randomized to proactive support of labour will stay at the hospital and have one-to-one midwife support. If no progression during the next 1–2 hours, amniotomy and/or oxytocin stimulation will be started. The control group will adhere to the standard procedures for labour support: expectance until established regular contractions and 4–5 cm cervical dilatation, and then one-to-one midwife support.

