Proactive support of labour was developed by Reuwer et al., in the Netherlands, with the purpose of preventing exhausting and prolonged labour and to facilitate a good birth experience in healthy nulliparous women [7]. Proactive support of labour focuses on the early stage of labour, the latent phase. It defines the start of the active phase of labour as 1–3 cm cervix dilatation, fully effaced cervix (< 5 mm) and painful contractions. Progress in labour is expected at this time, 1 cm per hour, according to Friedman’s curve [13]. Slow progress in the first 3 hours is a clear indication of ineffective contractions. If there is no progression during the next 1–2 hours, stimulation of the contractions should be started first with amniotomy and followed by oxytocin stimulation administered intravenously, after 1–2 hours, if regular contraction are lacking. The idea behind proactive support of labour is that intervention should be initiated early, in latent phase, (before 4 cm dilatation and regular contractions) when there is indication of slow progress. High-quality labour support includes a clear diagnosis of labour and early detection and correction of dysfunctional labour [7].

Proactive support of labour requires good communication throughout the entire process; it includes pre-labour education, psychological support, continuous personal attention and commitment. One-to-one continuous midwife support is already mandatory in early labour [7].

.Nulliparous and multiparous women have different prognoses in terms of birth progression and risk of operative birth [14]. Reuwer et al. emphasize the fundamental differences between the first and subsequent deliveries [7]. A prolonged latent phase in nulliparous women is caused by inefficient uterine contractions in about 10% of cases. Interventions have better effect in early labour, before the mother, uterus and fetus are exhausted [5]. According to Reuwer et al., labour is hard work and should take only one “working day” [7].

Today, labour support is similar in nulliparous and multiparous women. Most women in the latent phase are sent home for expectance and asked to contact the ward when the contractions increase. Active labour is defined as regular contractions and cervical dilatation of 4–5 cm [12].

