##### Statistical analyses of data

We will report data both as intention to treat and as per protocol. Per protocol data results will be considered as the clinically relevant, as the study is based on two different protocols for management of labour. The statistical program IBM SPSS Statistics for Windows version 25 will be used (IBM Corp., Armonk, NY, USA). We will report missing data as missing data. No imputation will be made.

Differences between categorical variables will be analysed by Pearson chi-square test.

*P* values < 0.05 are considered statistically significant. Continuous variables will be analysed by odds ratio and standard mean differences. Confidence intervals will be reported.

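### Only crude comparisons are planned, although BMI stratum, age and cervical dilatation at entry are known before randomisation: a missed gain in precision, not an error

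*Protocol article*

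**What the plan says.** Under Statistical analyses of data, the protocol article states that "Differences between categorical variables will be analysed by Pearson chi-square test". Normal delivery, a primary outcome, falls under this rule. For continuous outcomes it states: "Continuous variables will be analysed by odds ratio and standard mean differences". An odds ratio does not apply to a continuous variable, so I read this as mean differences for duration of labour, the first secondary outcome. No covariate and no regression model is named. Both intention-to-treat and per-protocol results are to be reported; this point concerns the intention-to-treat analysis.

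Three pre-randomisation values appear elsewhere in the article:

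- **BMI.** Assignment of interventions and collection stratifies randomisation by first-trimester BMI in three classes, on the ground that obesity affects nearly every aspect of pregnancy and labour. BMI has no stated role in the analysis.
- **Age.** Study variables gives the list: "Baseline variables are: (1) age, (2) civil status, (3) education and (4) former gynecological history". Age has no stated role in the analysis.
- **Cervical dilatation at entry.** The Abstract gives eligibility as "Robson group 1, with painful contractions, and fully effaced cervix, with 1–3 cm dilatation". Dilatation is therefore assessed before entry, but it is not in the baseline list.

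**The concern.** A crude comparison leaves the variation due to known prognostic factors in the error term. If a factor happens to be unbalanced between arms, part of that imbalance shows up as an apparent treatment difference. Adjusting for prespecified pre-randomisation values reduces both effects without more women or more examinations.

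Entry dilatation is the natural candidate in this trial. Background says, of labour under the proactive definition, "Progress in labour is expected at this time, 1 cm per hour". On that figure, entry at 1 cm rather than 3 cm means about 2 hours more labour still to run. Interventions also ties care to dilatation: hourly assessment up to 3 cm in the proactive arm, and active labour declared only at 4–5 cm in the control arm. The sponsor already accepts the principle for BMI, which it stratified to limit uneven allocation. The stated analysis then uses neither BMI nor the other two values.

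At stake is the width of the confidence intervals for normal delivery and duration. The outcomes are open-label, so a covariate added after results are seen would look post hoc. The choice has to be made beforehand to be credible.

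**Working it through.** **1. The plan's own figure.** Power calculation says: "To detect a 50% reduction in pathological births in the proactive group with 80% power, we will need 120 women in each group". The control rate there is 30%, so the comparison is 30% against 15%. The threshold is "values < 0.05 are considered statistically significant"; sidedness is not given, and I take it as two-sided.

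n = [1.96 × √(2 × 0.225 × 0.775) + 0.842 × √(0.30 × 0.70 + 0.15 × 0.85)]² / 0.15² = 121 per group.

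The unpooled formula gives 118. Power at 120 per group is 79.8%. The stated 120 therefore reproduces, and it rests on the unadjusted test.

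**2. Normal delivery: gain from adjustment.** Prognostic strengths are assumed, because the documents give none.

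*Simulation A:* 120 per arm, 4,000 runs for power, age standard normal, dilatation spread evenly over 1, 2 and 3 cm.

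| OR per SD of age / per cm | Crude power | Adjusted power | Gain (points) |
|---|---|---|---|
| 1.3 / 0.8 | 80.8% | 81.3% | 0.5 |
| 1.5 / 0.6 | 80.8% | 83.3% | 2.5 |
| 1.7 / 0.5 | 80.7% | 84.8% | 4.1 |

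*Simulation B:* 120 per arm, 3,000 runs, one normal covariate.

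| log OR per SD | Crude power | Adjusted power | Gain (points) |
|---|---|---|---|
| 0 | 80.9% | 80.4% | −0.6 |
| 0.3 | 81.1% | 81.3% | 0.1 |
| 0.6 | 80.6% | 82.0% | 1.4 |
| 1.0 | 79.8% | 85.4% | 5.6 |

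The simulation error of each power in B is about √(0.8 × 0.2 / 3000) = 0.7 points.

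*Approximation:* effective n per arm = 120 / (1 − R²). Power is 80.6% at R² = 0.02, 81.8% at 0.05 and 83.9% at 0.10. At 0.20 it is 87.9%, but the strongest simulated setting (85.4%) lies between 0.10 and 0.20, so 0.20 is beyond what was simulated.

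**3. Type I error.** Null rejection in A was 4.8–5.6% crude and 5.2–5.8% adjusted. In B the crude test rejected in 4.8–5.7% of runs at every covariate strength. The crude test is sound.

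**4. Duration of labour.** Assume an SD of 4 h, an even spread over 1, 2 and 3 cm (SD = √(2/3) = 0.816 cm), and timing from entry in both arms.

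R² = (hours per cm × 0.816)² / 4²; sample-size equivalent = 1 / (1 − R²).

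- 1 h per cm: 0.667 / 16 = 4%, equal to about 4% more women.
- 2 h per cm: 2.667 / 16 = 17%, equal to 20% more.
- 3 h per cm: 6 / 16 = 38%, equal to 60% more.

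Only the first slope has a source in the article.

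**5. Chance imbalance.** With one third of women entering at 3 cm, the SD of the between-arm difference in that share is √(2 × 1/3 × 2/3 / 120) = 6.1 points, so a difference above 10 points has probability 10%. If the 10 points come wholly from women at 1 cm, mean dilatation shifts by 0.10 × 2 = 0.2 cm. At 1 cm per hour that is 12 minutes, or 0.2 / 4 = 0.05 of the assumed SD.

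**6. Can the data carry the model?** Expected pathological births are 120 × 0.30 + 120 × 0.15 = 54. Arm, two BMI indicators, age and dilatation in cm make five coefficients, about 11 events each.

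**The case against.** The strongest reply is that nothing is wrong. An unadjusted comparison in a randomised trial is valid, it agrees with the way the trial was sized, and a fuller analysis plan that is not shown may add covariates. The validity argument stands in full, and it limits the point to efficiency. The point survives because the article names a crude method, so there is a stated choice to improve on.

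Four stronger readings are tempting, and the documents do not support them:

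- *That the comparison has no protection against chance imbalance.* Allocation is randomised and stratified by BMI. What is missing is protection specific to age and dilatation.
- *That a woman entering at 1 cm starts two hours behind in either arm.* The 1 cm per hour belongs to the proactive definition of labour. Controls at 1–3 cm are classed as latent and usually go home. The article does not say when the duration clock starts; if it starts at 4–5 cm for controls, entry dilatation need not lengthen their recorded duration.
- *That adjustment is worth 20% or 60% more women.* Those figures need slopes of 2 or 3 h per cm, which appear nowhere in the article.
- *That dilatation goes unrecorded.* BMI is absent from the same baseline list although it must be held for stratification, so the list is not exhaustive. Collection of data says that all relevant data enter the CRF.

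It is also fair that BMI is the only factor the article itself justifies as prognostic in these women. Any adjustment model should therefore include it first.

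**Conclusion.** The point holds as a missed and nearly free gain in precision. It is not an error, and it does not threaten the validity of the intention-to-treat test.

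For normal delivery the gain at 120 per arm is roughly 0 to 5 percentage points of power (5.6 at the strongest simulated setting, and a loss of about half a point, within simulation error, if the covariate predicts nothing). For duration, entry dilatation explains about 4% of the variance at 1 h per cm. It explains more only if the slope is steeper, and it matters in this way only if duration is timed from entry in both arms.

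These sizes rest on assumed prognostic strengths, an assumed even spread of entry dilatation and an assumed SD of 4 h. The documents supply only the 30% and 15% rates, the 120 per group, the 1–3 cm range and the 1 cm per hour. A reader might infer that the planned analysis is biased or the trial undersized for lack of adjustment; steps 1 and 3 of the working show neither.

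**What to change.** In Statistical analyses of data, prespecify that:

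- the intention-to-treat analysis of normal delivery uses logistic regression on arm, BMI stratum, age and cervical dilatation at entry (cm), reported as a standardised risk difference with confidence interval, so that the result is not a conditional odds ratio;
- duration of labour uses a linear model with the same covariates, reported as a difference in hours with confidence interval;
- the crude chi-square is kept as a supporting result.

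In Study variables, add cervical dilatation at entry to the baseline variables.

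The cost is slightly more analysis work and at most one field copied from the admission record, since dilatation is already assessed for eligibility. The SPSS version named in the article fits both models; the standardised risk difference and its interval take a short extra step. No extra women or examinations are needed. The wording should be fixed before outcomes are compared by arm.

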### Study hypotheses

H^0^: Women randomized to proactive labour support versus those randomized to standard labour support have similar rate of normal deliveries.

H^0^: Women randomized to proactive labour support versus those randomized to standard labour support have no difference in birth experience.

H^1^: Women randomized to proactive labour support have a higher rate of normal deliveries compared to those in the standard labour support group.

H^2^: Women randomized to proactive labour support have better birth experience compared to those in the standard labour support group.

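### As written, ordered CEQ answers and categorised VAS scores go to an unordered Pearson chi-square, which loses power and does not by itself show a better birth experience

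*Protocol article*

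**What the plan says.** All references are to the protocol article.

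- *Primary outcome* lists birth experience on the CEQ as the second of two primary outcomes. *Study hypotheses* sets a null of no difference in birth experience and the alternative H2: "Women randomized to proactive labour support have better birth experience compared to those in the standard labour support group".
- *Study variables* describes the data: "The CEQ includes 22 items formulated as positive and negative statements". Answers are on four ordered levels from total agreement to total disagreement, and each item yields one variable. Pain memory, security and control are recorded on a visual analogue scale, and then "The VAS scores will be transformed to categorical values". Neither the number of categories nor the cut points are given.
- *Statistical analyses of data* states one test for such data: "Differences between categorical variables will be analysed by Pearson chi-square test". Continuous variables are to be reported by odds ratio and standard mean difference, with confidence intervals. The significance rule is that P "values < 0.05 are considered statistically significant". No method that uses the order of categories is named.
- *Interventions* describes four CEQ dimensions but does not say that dimension scores are what will be compared.

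**The concern.** Four-point agreement items are ordered, and so is a VAS after it has been cut. The Pearson chi-square treats the levels as unordered labels. This has two consequences for an outcome whose hypothesis is that experience is better.

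First, a significant result says only that the two distributions differ. They may differ because answers spread out, with no movement towards better or worse. Second, the test spreads its sensitivity over every way in which four proportions can differ. It is therefore less able to detect the one pattern H2 predicts, a consistent shift. Cutting the VAS discards further information that has already been collected.

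This matters more because the only power calculation concerns the other primary outcome, so nothing shows that the CEQ comparison has power to spare.

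**Working it through.** **The plan's own figure.** *Power calculation* assumes 30% pathological births and states: "To detect a 50% reduction in pathological births in the proactive group with 80% power, we will need 120 women in each group". Taking 30% against 15%, two-sided 5% (sidedness is not stated), and mean proportion 0.225:

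n = [1.960·√(2·0.225·0.775) + 0.842·√(0.30·0.70 + 0.15·0.85)]² / 0.15² = 120.5, or 121 per group. Power at 120 per group is 79.8%.

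The stated figure is reproduced. It concerns delivery outcome only. The document gives no CEQ effect size, SD or answer distribution, so the inputs below are assumptions, with 120 per arm and two-sided 5% throughout.

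**Loss from ignoring order, in general.** A one-directional shift with 80% power on 1 df has non-centrality (1.960 + 0.842)² = 7.85. A four-level item compared between two arms by Pearson chi-square has 3 df and critical value 7.81. With non-centrality 7.85 its power is 64%. Restoring 80% needs non-centrality 10.90, and 10.90 / 7.85 = 1.39, so about 39% more women.

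**A single four-level item.** 10,000 simulated trials per setting under a common odds ratio (OR), with control proportions of 25/25/25/25%, 40/35/15/10% and 55/30/10/5%:

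| Common OR | Pearson chi-square (3 df) | Rank test |
|---|---|---|
| 1.5 | 23–28% | 35–41% |
| 1.9 | 52–62% | 69–78% |
| 2.0 | 58–70% | 75–85% |

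With no effect (OR 1), both tests reject in about 5% of trials.

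**A VAS item.** The standardised difference with 80% power on the uncut score is (1.960 + 0.842)·√(2/120) = 0.36. By simulation, with normal scores and four equal-frequency categories:

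- uncut, t-test: 80%
- four categories, rank test: 73%
- four categories, Pearson chi-square: 57%

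With a median split there are only two categories and no order to lose. The expected proportions are 42.8% and 57.2%, and power is about 60%. The loss therefore does not depend on choosing four categories.

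**Direction.** Take counts of 10/50/50/10 and 30/30/30/30 in two arms of 120. Expected counts are 20/40/40/20 in each arm. Each arm contributes 5 + 2.5 + 2.5 + 5 = 15, so chi-square = 30.0 and p is about 0.000001. The mean code is 300/120 = 2.5 in both arms, so nothing has moved towards better or worse.

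Conversely, 60/30/20/10 against 40/30/30/20 is a real shift. It gives chi-square = 9.33, p = 0.025, and the value is the same however the four levels are shuffled.

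**The case against.** **The plan does not say outright that the CEQ goes to the chi-square.** This stands as a caveat. The statistical section has one generic rule for categorical and one for continuous variables and names no instrument. If dimension scores were analysed as continuous, the mean-difference rule would apply and the item-level loss would not arise. But the text defines one variable per item, turns the remaining continuous responses into categories, and never says that a dimension score is compared. The chi-square is the plain reading.

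**A reader might infer that the plan cannot test a better experience at all.** The documents do not support that. The stated null is no difference, which a chi-square does test item by item, and direction can be read from the reported proportions. A non-directional test of a directional hypothesis is common. The defect is inefficiency, and a p-value that does not by itself establish improvement.

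**A reader might also infer that mixing positive and negative statements spoils the analysis.** It does not on this reading, because reversing an item's codes leaves its chi-square unchanged. Direction of scoring matters only if items are combined. The section gives a response format and cites the validated instrument, which may fix the reversal. Nothing says that raw codes will be averaged unreversed.

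**Categorising the VAS may be the instrument's own scoring step.** It may be, and this document cannot settle it. The fix allows for that.

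**The power figures rest on assumed inputs.** They do, and they are powers for single items, not for the CEQ outcome as a whole. They also assume that every woman returns the mailed form. The direction of the loss is the same in every setting tried with a real shift.

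**Conclusion.** The point holds as an avoidable loss on a primary outcome. Read plainly, the plan applies an order-blind test to ordered data and coarsens the VAS beforehand. Against a consistent shift, 80% power on 1 df becomes about 64% on 3 df. The simulated cost for a four-level item is about 12 to 18 percentage points for odds ratios of 1.5 to 2.0. For a VAS difference of 0.36 SD it is about 23 points (80% to 57%) if the scale is cut in four.

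This rests on reading the chi-square rule as covering CEQ items, on assumed effects and answer distributions, and on 120 returned questionnaires per arm. It does not show that the CEQ hypothesis is untestable or that the questionnaire will be mis-scored.

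**What to change.** In *Statistical analyses of data*, say how the CEQ is compared, in place of the Pearson chi-square. Scores should be compared by mean difference with a confidence interval or by a rank test, and single items by a rank test or a proportional-odds model. The chi-square can stay for genuinely unordered variables.

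In *Study variables*, state that the VAS items are analysed on their recorded scale, with categories used only where the questionnaire's own dimension scoring requires them.

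The cost is a few lines of wording. No new data, no change to the questionnaire and no extra women are needed. According to *Trial status*, recruitment was still open when the article was written, and *Study variables* plans no interim analyses, so the change could be made before any comparison of the arms.
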